## Experimental protocol

Participants will undergo all procedures described above on the day of initial evaluation and then the first intervention session will begin. Patients will be allocated according to groups in which they were randomly assigned. The group will be revealed when the envelope is opened by therapists.

## Study groups

Control group – treadmill gait training

The Gait Trainer System 2 (Biodex Medical Systems), which contains an electric treadmill with a walking area of 160 × 51 cm and an anterior bar, will be used for treadmill gait training (Fig. 2). This equipment allows one to change the speed with a minimum speed of 0.04 m/s and a maximum speed of 4.7 m/s, providing real-time data on speed and traveled distance. Associated with the treadmill is the partial weight support system (Unweighing System) consisting of a vest coupled to a body weight suspension mechanism. However, the vest will be used only for the purpose of providing safety and balance but will not provide any support [25].

**Fig. 2 Fig2:**
[figure not shown]
System for gait training: Gait Trainer System 2

The training protocol will follow what was used in a previous study, involving patients with subacute stroke, since the protocol used was safe and capable of increasing gait speed and distance covered on a treadmill [53]. In the first training session, participants will undergo a few minutes of treadmill training for familiarization and will be instructed to hold onto the anterior treadmill bar with their non-paretic hand to provide stability. The treadmill speed will be selected as the “maximum comfort”, meaning the maximum tolerated by the individual, while adequate posture is maintained throughout gait cycle without any compensation or muscle fatigue.

From the second session, participants will be encouraged to withdraw support from their non-paretic hand over the treadmill bar. In the following session, participants will be encouraged to increase the treadmill speed according to individual tolerance. Participants will be encouraged to achieve maximum speed at the beginning of the session. After reaching that speed, it will remain constant throughout the session. This procedure will be repeated at the beginning of all subsequent sessions.

The treadmill training sessions will last 30 min, and two small rest periods (about 3 min) will be allowed in the 10th and 20th minutes, which will not be counted in the total duration of the session. During these pauses, the therapists will monitor cardiovascular parameters, effort perception, and pain. However, HR will be monitored throughout the session so as not to exceed the maximum submaximal values (75% of maximum frequency) and so that training can occur by maintaining target frequency of 50% of maximum HR [14].

Before training (in rest), individuals will be assessed regarding cardiovascular parameters and will be reassessed in the 1st and 5th minutes after the end of the session by the study therapists. The control group will be submitted to training by treadmill during a 30-min session without inclination three times per week for 6 weeks.

Experimental group 1 - treadmill gait training with inclination of 5%

Participants in experimental group 1 will perform the same gait training described for the control group; however, the treadmill will have an anterior inclination equivalent to 5% [27]. The treadmill will be inclined gradually in the initial minutes of each session, and the speed will also be adjusted in accordance with the previously described protocol. Experimental group 1 will be submitted to treadmill training during 30-min sessions with an inclination of 5% three times per week for 6 weeks.

Experimental group 2 - treadmill gait training with inclination of 10%

Participants in experimental group 2 will perform the same gait training described for the control group; however, the treadmill will have an anterior inclination equivalent to 10% [28]. The treadmill will be inclined gradually in the initial minutes of each session, and the speed will also be adjusted in accordance with the previously described protocol. Experimental group 2 will be submitted to treadmill training during 30-min sessions with an inclination of 10% three times per week for 6 weeks.

All participants (of the three groups) will be instructed not to perform any other type of aerobic activity or gait training during the study period. All participants will be called by phone to confirm each training session and all of the evaluations (especially the follow-up). The schematic study design is shown in Fig. 3.

**Fig. 3 Fig3:**
[figure not shown]
The schematic study design

## Statistical analysis

Data analysis will be carried out by a blinded evaluator regarding group allocation by using the Statistical Package for the Social Sciences software (SPSS, IBM, Armonk, NY, USA) for Windows. Only the main study researcher (not involved in data collection) can make the final decision to stop the trial and will have access to the final data.

Descriptive analysis of the sample characterization variables will be performed through central tendency and dispersion measures. Inferential analysis will consider statistical significance of 5% for all studied variables. Mixed analysis of variance (ANOVA) with repeated measures will be used to compare values and variations of outcome measures, comparing values between groups and between baseline, post-training, and follow-up assessments. Normality tests (Shapiro–Wilk) will be used for outcomes and will be compared between groups within each training session by using intergroup comparisons, *t* tests for independent samples, or Mann–Whitney tests.

Group description will be presented as mean and standard deviation, and the effect size and the 95% confidence interval will be reported. Intention-to-treat analysis will be performed for dropout data, considering the last data obtained from the participant.

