### Sample size

Sample size was calculated by using an online calculator [31], and the variable gait speed (in meters per second) was adopted as the primary outcome measure. According to a previous study involving individuals with post-stroke hemiparesis who performed treadmill training with partial weight support and anterior inclination of 10° (experimental) and no inclination (control) [26], standard deviations observed in the experimental and control groups were 0.1 and 0.2, respectively. The sample size was calculated from these data to detect a difference in gait speed between the groups of 0.18 m/s (α = 5% and power = 80%) since the minimum detectable difference in the gait speed for patients with chronic stroke was 0.18 m/s [32]. A ratio between the control and experimental groups of 1:2 was considered, as it was verified that the smallest numbers needed to detect the expected difference would be 8 individuals in the control group and 16 individuals in the experimental group, totaling 24 participants. Given a dropout rate of about 40%, a sample total of 36 participants (12 in the control group and 24 in the experimental group) was determined.

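### Gait speed at baseline is a repeated level of the mixed ANOVA rather than a covariate, and no deciding term is named; the cost in power depends on an unstated correlation and on the term tested

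*Protocol article*

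**What the plan says.** The Statistical analysis section of the protocol article fixes the model: "Mixed analysis of variance (ANOVA) with repeated measures will be used to compare values and variations of outcome measures". The four assessments listed under Evaluation procedures (baseline, post-training, 30 days, 1 year) make this a design of three groups by four times. Baseline is a level of the time factor, because the section describes the model as "comparing values between groups and between baseline, post-training, and follow-up assessments". The section does not say whether the group main effect, the group-by-time interaction or a contrast at one visit answers the research questions. It names no pairwise procedure for this model. On error rates it says "Inferential analysis will consider statistical significance of 5% for all studied variables".

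The Sample size section plans on gait speed "to detect a difference in gait speed between the groups of 0.18 m/s". It takes from a previous study that "standard deviations observed in the experimental and control groups were 0.1 and 0.2, respectively", which is a fourfold ratio of variances. The Background asks two questions: whether incline helps compared with no incline, and which degree of incline is better.

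**The concern.** Baseline gait speed is measured on every participant before training, yet the stated model treats it as one more outcome. Two losses can follow. A between-groups test averaged over all visits includes one at which treatment cannot have acted. A comparison of change from baseline subtracts the whole baseline value, where regression on baseline would remove only the part that predicts the outcome. With 12 per arm before dropout, avoidable loss of precision matters.

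A mixed ANOVA also conventionally uses one error variance for all groups, while the planning SDs differ by arm. If pairwise comparisons use that pooled error, the tests for the two research questions would err in opposite directions.

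**Working it through.** **Inputs from the protocol.** 12 per arm; difference 0.18 m/s; SDs 0.2 (control) and 0.1 (experimental); 5% significance, taken as two-sided; four assessments.

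**Assumptions not in the protocol.** r is the correlation between gait speeds at any two visits (compound symmetry), over the range 0.3 to 0.8. The 0.18 m/s is present in both inclined arms and sustained at all three later visits.

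**The plan's own figure.** The Sample size section states "8 individuals in the control group and 16 individuals in the experimental group, totaling 24 participants". With one common SD, √((0.2² + 2 × 0.1²)/3) = 0.141, the control group needs 0.02 × 1.5 × (1.96 + 0.84)²/0.18² ≈ 7.3, so 8 + 16. Exchanging the two SDs between arms gives the same result. With the SDs as labelled it is (0.04 + 0.01/2) × (1.96 + 0.84)²/0.18² ≈ 10.9, so 11 + 22. The stated size is thus reproduced with a common variance or exchanged SDs, and not with the SDs as labelled. That is a separate matter. It does not show which term of the ANOVA was meant to decide.

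**Dilution in the main effect.** (0 + 0.18 + 0.18 + 0.18)/4 = 0.135 m/s. If the effect were present only at post-training it would be 0.18/4 = 0.045 m/s.

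**Variance per participant, in units of σ².** Baseline-to-post change: 2(1 − r). Baseline-adjusted post value: 1 − r². Ratio: 2/(1 + r), which is 1.54, 1.33, 1.18 and 1.11 at r = 0.3, 0.5, 0.7 and 0.8.

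The mean of four visits has variance (1 + 3r)/4, which rises with r. The squared effect over this variance is therefore 0.135²/0.475 = 0.038 at r = 0.3, against 0.18²/0.91 = 0.036 for ANCOVA. At r = 0.7 it is 0.135²/0.775 = 0.024 against 0.18²/0.51 = 0.064. This is why the main effect does slightly better at low r and much worse at high r.

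**Simulated omnibus power, 12 per arm, common SD 0.2** (agreement between runs within about 2 points):

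| r | ANCOVA at post-training | Baseline-to-post change | Four-visit interaction | Four-visit main effect |
|---|---|---|---|---|
| 0.3 | 61% | 44% | 43% | 67% |
| 0.5 | 71% | 59% | 60% | 54% |
| 0.7 | 85% | 80% | 84% | 44% |
| 0.8 | 96% | 94% | 97% | 41% |

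**The same with SDs 0.2/0.1/0.1 at every visit:**

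| r | ANCOVA at post-training | Baseline-to-post change | Four-visit interaction | Four-visit main effect |
|---|---|---|---|---|
| 0.3 | 84% | 68% | 72% | 88% |
| 0.5 | 90% | 82% | 86% | 77% |
| 0.7 | 97% | 95% | 98% | 68% |
| 0.8 | 99.5% | 99% | 99.9% | 65% |

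The pattern is the same at a higher level. ANCOVA gains 12 points over the interaction at r = 0.3, 4 at r = 0.5, and nothing from 0.7.

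**Pooled error under the planning SDs.** Pooled variance = (0.04 + 0.01 + 0.01)/3 = 0.02, so every pairwise difference is judged against 2 × 0.02 = 0.04.

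- Control against one incline: the true sum is 0.04 + 0.01 = 0.05. The standard error is too small by √(0.04/0.05) = 0.89. The effective cut-off is 1.96 × 0.89 ≈ 1.75, or about 8%.
- 5% against 10%: the true sum is 0.02. The standard error is too large by √2. The effective cut-off is about 2.77, or under 1%.

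Simulation gives about 8% and 1%; Welch tests give about 5% for both. If baseline SDs are equal and only later SDs differ, pooled tests on change scores give about 6.5% and 2.6%. The omnibus F tests are only mildly inflated, at about 6 to 7%. ANCOVA with a pooled variance still gives about 8.3% and 1%, so baseline adjustment alone does not repair the pairwise error rates.

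**The case against.** A repeated-measures ANOVA with baseline as a level is a valid analysis of a randomised trial, so preferring ANCOVA is advice on efficiency. The deciding contrast and the post-hoc test may be set out in an analysis plan that is not shown. Both points stand. They make this a recommendation on a stated choice of model, and the missing post-hoc detail is not itself a fault.

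Several stronger readings are tempting and are not supported:

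- *That the group main effect has only about 21 to 23% power.* That holds for a model with baseline and post-training alone. The protocol plans four visits, for which the figure is about 41 to 67% with a common SD of 0.2.
- *That the group-by-time test is the same as an unadjusted change score.* That is true of two visits. The four-visit interaction also draws on the follow-ups and matches post-training ANCOVA from about r = 0.7.
- *That the plan prescribes tests with wrong error rates.* The pooled error is inferred from the usual form of the method, since the protocol names no pairwise test for this model. The SDs come from another study, and randomisation gives no reason for arms to differ in SD at baseline.
- *That power for 5% against 10% falls from 80% to 53%.* This needs a true difference of 0.12 m/s, which the protocol does not give.

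**Conclusion.** The point holds as a moderate recommendation. The model in the Statistical analysis section puts baseline among the outcomes and leaves open which term decides.

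With a common SD of 0.2, the loss against baseline-adjusted analysis at post-training is about 18 points at r = 0.3 and 11 at r = 0.5 if the interaction decides, and negligible from about r = 0.7. If the main effect decides, the loss is about 17 points at r = 0.5 and 41 at r = 0.7. At r = 0.3 the main effect is slightly ahead, provided that the effect lasts the full year. No single figure for the loss can be drawn from the documents, because r is not given.

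The error-rate part is conditional on the planning SDs holding and on a pooled pairwise test being used. It justifies a low-cost safeguard and does not establish an error in the plan.

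**What to change.** Amend the Statistical analysis section in three ways.

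1. Treat the post-training, 1-month and 1-year values as responses, with the participant's own baseline value as a covariate. Make ANCOVA at post-training the deciding analysis for gait speed, and carry the same covariate into the longitudinal model.
2. State that the conclusion rests on the group contrast at post-training and not on the group main effect.
3. Use unequal-variance standard errors (Welch-type or HC3) for pairwise contrasts.

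With arm-specific variances and 12 per arm, the adjusted control-against-incline test has a simulated type I error of 5.3 to 5.7%. Under the planning SDs its power is about 77, 85, 95 and 99% at r = 0.3, 0.5, 0.7 and 0.8. The matching unadjusted Welch test on change has 60, 75, 92 and 98%.

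The cost is a change of wording, one degree of freedom, and slightly lower pairwise power if the variances are in fact equal. No new data are needed. The change should be recorded before the analyst learns the group codes.

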**Methods:**

A single-blind randomized clinical trial will be conducted. The sample will consist of 36 patients, who will be allocated in three groups: control group (n = 12), experimental group 1 (n = 12), and experimental group 2 (n = 12). The intervention will occur for 6 consecutive weeks, three times a week, 30 min each session, in all groups. The control group will perform a treadmill gait training without inclination, experimental group 1 will perform a treadmill gait training with anterior inclination of 5%, and experimental group 2 will perform a treadmill gait training with anterior inclination of 10%. All participants will be assessed for sample characterization measures, gait speed, functional capacity, systemic arterial blood pressure, heart rate, peripheral oxygen saturation, exercise capacity, neuromuscular torque, and quality of life. Evaluations of outcome measures will occur at the end of the interventions (post-training) and after 1 month and 1 year after the end of the interventions (short- and long-term follow-up). Statistical analysis will be performed descriptively and inferentially. Alpha equals 5% will be considered for inferential analysis. Mixed analysis of variance with repeated measures will be used to compare outcome measures between groups and between baseline, post-training, and follow-up. Normality test (Shapiro–Wilk) and subsequently *t* test (or Mann–Whitney) will be used to compare groups during the same training session.

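### Three groups are compared within each training session by two-sample tests at a flat 5%; if all pairs are tested, the chance of a false difference per variable over 18 sessions is roughly 27–84%

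*Protocol article*

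**What the plan says.** The Statistical analysis section describes two separate analyses.

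- **Study visits.** A mixed repeated-measures ANOVA "will be used to compare values and variations of outcome measures, comparing values between groups and between baseline, post-training, and follow-up assessments". This method accommodates three groups.
- **Training sessions.** After a Shapiro–Wilk test, outcomes "will be compared between groups within each training session by using intergroup comparisons". The methods named are t "tests for independent samples, or Mann–Whitney tests". The Methods part of the Abstract repeats the plan: the t test or Mann–Whitney test "will be used to compare groups during the same training session".

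One threshold covers everything: "Inferential analysis will consider statistical significance of 5% for all studied variables". No three-group test, post hoc procedure or adjustment is named for the session data.

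The Abstract gives three groups of 12 and the schedule: "The intervention will occur for 6 consecutive weeks, three times a week, 30 min each session, in all groups". Under Study groups, the cardiovascular values are taken before each session, when "individuals will be assessed regarding cardiovascular parameters and will be reassessed in the 1st and 5th minutes after the end of the session". They are also monitored in the two pauses.

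**The concern.** A two-sample test cannot answer a three-group question in one step. Following the text means choosing pairs, and covering all of them takes three tests per variable per session, repeated over the training course, each at 5%. The text also lets the Shapiro–Wilk result, on about 12 values per group, decide between the t test and the Mann–Whitney test. The method could then differ from one session to the next for the same variable.

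At stake is how the session data are read. The Background asks whether inclined training is effective and safe compared with no inclination, and which inclination is most effective. Cardiovascular values recorded at each session bear directly on load and tolerance. A scatter of unadjusted session p-values would not separate a real effect of incline from chance.

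**Working it through.** **Inputs from the protocol.** Three groups of 12; 6 weeks × 3 sessions = 18 sessions; 5% per test. The protocol states no error rate for the session tests as a set, so there is no figure to reproduce beyond the nominal 5%.

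**Assumptions.** Two-sided tests; all pairs tested at every session; no true difference; normally distributed values. The correlation between sessions within a participant is not in the protocol and is shown as a range.

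**Number of tests per variable.**
- Pairs among three groups: 3 × 2 / 2 = 3.
- Over all sessions: 3 × 18 = 54.
- Expected false positives: 54 × 0.05 = 2.7, whatever the correlation.

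**If all tests were independent** (1 − 0.95^m):
- m = 3 (one session): 14.3%.
- m = 18 (one pair, all sessions): 60.3%.
- m = 54 (all pairs, all sessions): 93.7%.

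The tests are not independent. Pairs share a group, and the same participants attend every session.

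**Simulation with both dependencies.** 6,000 null trials of 3 × 12 participants and 18 sessions, with t tests on 12 + 12 − 2 = 22 degrees of freedom. The Monte Carlo standard error is at most √(0.25/6,000), about 0.65 percentage points. Within one session, the three pairwise tests give at least one false difference in about 12% of trials. Over 18 sessions, for one variable:

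| Constant correlation between sessions | All three pairs (54 tests) | One pair only (18 tests) |
|---|---|---|
| 0 | 91% | 60% |
| 0.3 | 84% | 51% |
| 0.5 | 72% | 40% |
| 0.7 | 55% | 29% |
| 0.8 | 46% | 23% |
| 0.9 | 34% | 15% |
| 0.95 | 27% | 12% |

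**Sensitivity.**
- If correlation decays with the gap between sessions (first-order autoregressive), the all-pairs figures are 80% at 0.7 and 58% at 0.9.
- With 8 per group, the evaluable 24 of the Sample size section divided by three, the all-pairs figures hardly move: 56%, 46% and 33% at constant correlations of 0.7, 0.8 and 0.9.
- For an illustrative four variables, with an assumed correlation of 0.3 between them, the chance of any false difference is 99%, 94%, 89% and 78% at session correlations of 0.5, 0.7, 0.8 and 0.9. The number four is an assumption, since the protocol does not say how many variables or time points will be tested.

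**Would a three-group test at each session suffice?** No. Eighteen unadjusted omnibus tests would still give 60.3% if independent. A Bonferroni limit over the 54 tests would be 0.05/54 = 0.00093 per test.

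The effect of switching between the t test and the Mann–Whitney test was not simulated. It is a point about consistency of method and adds nothing to the figures above.

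**The case against.** The best defence is that this is a condensed article. Which sessions and pairs are tested, and with what adjustment, could sit in a fuller plan, and the sentence in the Statistical analysis section is poorly constructed. That answers silence on adjustment, but not what is stated: two-sample tests for three groups, within each session, at 5% for all variables. A fuller plan would have to change this text, not merely add to it.

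Several limits do stand. A reader might infer the following stronger points, which the protocol does not support:

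- **That false session differences are nearly certain.** For one variable this needs all 54 tests and independent sessions (91–94%). The same participants are measured each time, so the rate is lower. It approaches certainty only when several variables or time points are pooled, and the protocol does not fix that count. Perceived effort and pain, for example, are listed as monitoring measures, apart from the outcomes.
- **That every significant session result would be spurious.** The calculation assumes no true difference. Participants train at 0%, 5% or 10% incline, so heart rate during training may genuinely differ.
- **That each test is invalid because it ignores repeated measures.** Within one session, each test compares different participants. The fault is multiplicity across pairs and sessions.
- **That the main results are compromised.** Comparisons of baseline, post-training and follow-up, including gait speed, on which the sample size rests, use the separate mixed ANOVA.

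**Conclusion.** The session-level rule is wrong as written and should be changed. It applies two-group tests to three groups at each of 18 sessions, at 5% with no adjustment stated. If all pairs are tested and there is no true difference, the error rate is about 12% per variable per session. Over the training course it is roughly 27–84% per variable, for assumed constant correlations of 0.95 to 0.3. Even at 0.95 it is more than five times the nominal 5%, and testing a single pair throughout would still give 12%. The range is wide because the correlation is unknown, but no value examined brings the rate near 5%. The consequence is confined to conclusions drawn from individual sessions.

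**What to change.** Replace the session tests with one linear mixed model per variable over all 18 sessions.

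- **Terms:** group (three levels), session, group × session and a random participant effect. Add as covariate the resting value taken before the first session, where one is recorded. Do not use each session's starting value: from the second session it is measured after randomisation and may already reflect training, and the Discussion expects training to lower heart rate and blood pressure.
- **Tests:** the overall group effect and the group × session term, each at 5%. Two such tests per variable would give 1 − 0.95² = 9.75% if independent, against the 27–84% above.
- **Pairwise contrasts:** only if the relevant overall test is significant. With three groups this protects the contrasts on the group effect. It does not fully protect contrasts at individual sessions after a significant interaction.
- **Normality:** drop the Shapiro–Wilk switch between tests.
- **Labelling:** call the session-level results exploratory, because multiplicity across variables remains. Four independent 5% tests, for example, give 1 − 0.95⁴ = 18.5%.

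The cost is revised wording and somewhat more analysis work. It needs no new data, and SPSS, which the protocol already names, can fit the model. Fewer session results will be nominally significant.

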### Randomization and blinding

Randomization sequence will be generated by computer [38], and three groups with blocks of 12 participants will be considered. This stage will be conducted by a researcher not involved in the study. This researcher will keep the randomization list confidential until the end of the study and will organize the allocation in sequentially numbered opaque envelopes. These envelopes will be sealed, and the randomization sequence will be according to the coding that will be created for study groups (control, experimental 1, and experimental 2).

The content of each envelope will be revealed only at the beginning of the training of each patient by study therapists in order to maintain allocation confidentiality. The same therapists involved in control group training will perform training in the experimental groups. Sample characterization measures and outcome measures will be evaluated by masked researchers in relation to group allocation. These researchers will be the same as those who enrolled participants in the study.

Only variables that will be collected during the training will be evaluated by study therapists (non-blind). Statistical analysis will be performed by one researcher, who will be blind to the allocation of patients in groups. Data will be tabulated with a predetermined encoding by another blinded evaluator, who will also check data (range check for data values). The present protocol has been prepared in accordance with relevant items from the SPIRIT (Standard Protocol Items: Recommendations for Interventional Trials) checklist (Additional file 1) and the SPIRIT figure (Fig. 1).

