## Evaluation procedures

The researchers will be trained before data collection procedures to ensure the reliability of measurements. It is important to highlight that these researchers will remain blind to group allocation throughout the study period.

Previously contacted patients with stroke or those who spontaneously search for the study will be evaluated according to inclusion criteria at our laboratory, where they will be informed about the research objectives and procedures to be carried out. Once they agree to participate in the study, they will be asked to sign a consent form.

The participants will first be submitted to a general approach to obtain clinical, demographic, and anthropometric data, and other measures of sample characterization will also be collected. Furthermore, the following outcome variables will be evaluated: gait speed, functional capacity, and muscle torque. Participants will subsequently remain at rest, sitting for at least 15 min. During this period, quality of life will be evaluated. Lastly, cardiovascular parameters will be obtained (at rest).

Outcome measures will be collected again at the end of the interventions (post-training), after 30 days of the end of the interventions (short-term follow-up), and after 1 year of the end of the interventions (long-term follow-up). Adverse events will be evaluated at follow-up.

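### Session HR, BP and SpO2 are compared between arms of 12 by tests that ignore the resting value already taken before allocation is revealed

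*Protocol article*

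**What the plan says.** The protocol article describes two inferential analyses under Statistical analysis. The first is a mixed ANOVA of the outcome measures over baseline, post-training and follow-up. The second concerns training sessions: outcomes "will be compared between groups within each training session by using intergroup comparisons", with t tests for independent samples or Mann-Whitney tests after a Shapiro-Wilk check. The Abstract repeats both. On alpha, the section says "Inferential analysis will consider statistical significance of 5% for all studied variables".

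The session data come from the therapists, who are not blind. Under Study groups (control group, whose procedure the other arms share): "Before training (in rest), individuals will be assessed regarding cardiovascular parameters and will be reassessed in the 1st and 5th minutes after the end" (that is, once training stops). Readings are also taken in the two pauses.

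A separate resting value exists. Evaluation procedures ends the initial assessment with "Lastly, cardiovascular parameters will be obtained (at rest" after at least 15 minutes of sitting, and outcome measures are taken by masked researchers. Experimental protocol gives the order: "Participants will undergo all procedures described above on the day of initial evaluation and then the first intervention session will begin". Randomization and blinding adds: "The content of each envelope will be revealed only at the beginning of the training of each patient by study therapists".

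**The concern.** Neither a t test nor a Mann-Whitney test can carry a covariate, and the plan names no change from rest for this comparison. The same variable's resting value, recorded before anyone at the site knows the allocation, is left unused.

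Two things are at stake. If session values track a participant's resting level, the unadjusted test spends its small sample on variation between people that was already measured. And the same people are compared at every session. If one arm happens to start with a higher resting heart rate, part of that gap reappears each time, and a reader may take agreement across sessions as replication of an incline effect.

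**Working it through.** The plan states no power, SD or detectable difference for the session comparisons (its only power figure is for gait speed), so there is no figure to reproduce.

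**Inputs from the protocol article.** Arms: "control group (n = 12), experimental group 1 (n = 12), and experimental group 2 (n = 12" (Abstract). Sessions: "30-min session without inclination three times per week for 6 weeks" (Study groups), so 3 × 6 = 18. Alpha is 5%, taken as two-sided because the section does not say.

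**Assumptions, not in the documents.** SD of heart rate 12 bpm at rest and in session, a true difference of 10 bpm, and correlation r between initial resting value and session value from 0 to 0.8.

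**Step 1: power per session, 12 v 12 (noncentral t).**

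- Unadjusted: 22 df, noncentrality 10 / (12 × √(2/12)) = 10 / 4.90 = 2.04; power 50%. The difference detectable with 80% power is 1.197 SD, or 14.4 bpm.
- Adjusted (ANCOVA): residual SD = 12 × √((1 − r²) × 1.05) on 21 df. The factor 1 + 1/(2 × 12 − 4) = 1.05 is the approximate small-sample price of estimating the covariate slope.

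| r | residual SD (bpm) | noncentrality | power for 10 bpm |
|---|---|---|---|
| unadjusted | 12.0 | 2.04 | 50% |
| 0 | 12.3 | 1.99 | 48% |
| 0.2 | 12.0 | 2.03 | 49% |
| 0.3 | 11.7 | 2.09 | 51% |
| 0.5 | 10.6 | 2.30 | 59% |
| 0.7 | 8.8 | 2.79 | 76% |
| 0.8 | 7.4 | 3.32 | 89% |

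Without the 1.05 factor, power at 0.5, 0.7 and 0.8 would be 61%, 78% and 90%, so the penalty does not change the picture. Break-even lies at r of about 0.2 to 0.25.

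**Step 2: chance imbalance at rest.** The SD of the difference between two arm means is 12 × √(2/12) = 4.9 bpm. A gap of at least 5 bpm then has probability 31% for a given pair of arms and 56% for some pair of the three (22% and 44% if the SD is 10 bpm). The expected carry-over into each session is r × gap: 0.7 × 5 = 3.5 bpm at r = 0.7, but 0.3 × 5 = 1.5 bpm at r = 0.3.

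**Step 3: false positives with no true effect.** In a simulation of 6,000 two-arm trials (12 per arm, 18 correlated sessions), rejection rates per session were as follows. A resting imbalance above 0.5 SD (6 bpm at SD 12) occurs in 22% of trials for a pair of arms.

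| r | unadjusted, all trials | unadjusted, imbalance > 0.5 SD | adjusted, imbalance > 0.5 SD |
|---|---|---|---|
| 0.3 | 5.3% | 7.5% | 5.6% |
| 0.5 | 4.8% | 10.1% | 4.7% |
| 0.7 | 4.9% | 14.7% | 4.9% |
| 0.8 | 4.9% | 17.3% | 5.2% |

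**Step 4: clustering over 18 tests.** At r = 0.7 (correlation between sessions also 0.7), trials with any false positive average 3.0 of them unadjusted and 2.0 adjusted. However, the share of trials with at least one rises from 29% to 45%, because adjustment makes the session results less alike. A covariate alone therefore does not deal with 18 separate tests.

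**The case against.** Several points stand.

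- A reader might infer that the unadjusted tests are invalid. They are not: error per test is about 5% over all trials. The harm is lost precision, plus a bias conditional on an imbalance.
- A reader might take it as stated that absolute values are tested. The section names the tests, not the quantity. A t test could be run on change from rest, and readings before and after each session would allow that. But the reference to variations belongs to the sentence on the mixed ANOVA. That no change score is used here is an inference from the named tests.
- Because cardiovascular parameters are listed as primary outcomes, a reader might infer that the session tests are the trial's main evidence on incline. Nothing in the article says so. The mixed ANOVA tests the outcome measures, and the in-session readings also serve to monitor participants. The session tests are supporting.
- The correlation may be weak for in-session heart rate, which the protocol holds within age-based limits. The initial reading is also a single occasion, up to six weeks before the last sessions. Blood pressure and the pre-session and recovery values are not held in that way.

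One objection does not carry: that this is detail to be left to a full analysis plan. The article fixes the method, and the method named excludes a covariate.

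**Conclusion.** The point holds as a matter of efficiency and of conditional bias in a supporting analysis. The size depends on a correlation that the documents do not give. Under SD 12 bpm, a 10 bpm difference and full arms of 12, adjustment ranges from a loss of about 2 percentage points of power (50% to 48% at r = 0) to a gain of 26 points at 0.7 (50% to 76%) and 39 at 0.8 (50% to 89%). It is negligible at 0.3. The carry-over of a chance imbalance follows the same correlation. The figures are for heart rate; BP and SpO2 were not quantified. The visit-level mixed ANOVA is not touched. The change is worth making because the covariate is already collected and the possible loss is small.

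**What to change.** Under Statistical analysis, and in the matching sentence of the Abstract, replace the per-session t or Mann-Whitney tests for HR, BP and SpO2 by a comparison of arms that has the same variable's resting value from the initial evaluation as covariate.

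Preferably use one repeated-measures model across sessions for each variable and measurement time, with arm, session, arm by session and the initial resting value. This also replaces the 18 separate tests. With 36 participants, choose a simple covariance structure: an unstructured one over 18 sessions would need 18 × 19 / 2 = 171 parameters. If single-session comparisons are kept, use ANCOVA, or a rank-based ANCOVA where normality is doubtful.

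Do not make same-day pre-session rest the main covariate. From session 2 it is measured after randomisation and may carry a training effect. Report change from same-day rest descriptively, as the acute response.

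The cost is one degree of freedom for the covariate, revised analysis wording and a little more analysis work. No new data or visits are needed.
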